### Interim analyses {21b}

There are no interim analyses planned.

#### Methods or additional analyses (e.g., subgroup analyses) {20b}

To determine whether the results of the primary efficacy evaluation differ according to subgroups of study participants, a subgroup analysis will be performed. The subgroup analysis will compare participants with a usual pain intensity score over the past week at visit 2 of 50 points or higher to those with a score of 49 points or lower.

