### Outcomes {12}

The primary efficacy outcome of this trial is usual pain intensity score (VAS, 100 scale) at 8 weeks (V4). For secondary outcomes, see Table 1. For the method of aggregation, all outcome measures will be analyzed as continuous variables using mean values with appropriate statistical comparisons between groups (For further detail, see Statistical Analysis).

Through interviews, demographic information, medical history, surgical history, and prior/concomitant medications will be collected. Physical examination will include measurements of height, weight, and a patella examination. A knee X-ray will be taken to assign a K-L grade [40], which is used to assess exclusion criteria for osteoarthritis.

The usual and worst pain intensity scores assess the average and peak knee pain experienced over the past week, respectively. Participants mark their pain level on a visual analog scale from 0 to 100, with values recorded and rounded to the nearest whole number [41].

To assess knee function, participants complete the anterior knee pain scale (Kujala score), 13-item self-report questionnaire [42], with a total score calculated from the responses. Quality of life is assessed via the EQ-5D-5L [43] questionnaire, recording the sum of scores across five questions and today’s health status score. Depression severity is evaluated using the Patient Health Questionnaire-9 (PHQ-9) [44], with a total score from nine questions, while pain catastrophizing is assessed using the Pain Catastrophizing Scale (PCS) [45], totaling scores from 13 questions. Participants also rate their perceived recovery level on a 0 to 6 scale [46].

All pain and questionnaire assessments are conducted as electronic patient-reported outcomes (ePRO). Participants use digital tools provided at the site, with data automatically transferred to the electronic case report form (eCRF). For visit 3, if conducted as a televisit, participants may complete the assessments remotely.

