### Sample size {14}

The primary efficacy variable of this clinical trial is the intensity of usual pain over the past week at 8 weeks post-treatment initiation, aiming to assess whether the experimental group shows superior improvement compared to the control group. The hypothesis for the superiority test on the primary efficacy variable is as follows: $${H}_{0}: {\mu }_{t}={\mu }_{c} vs. {H}_{1}: {\mu }_{t}\ne {\mu }_{c}$$, where $${\mu }_{t}$$ represents the usual pain intensity at 8 weeks for the experimental group, and $${\upmu }_{\text{c}}$$ represents the same for the control group.

The sample size was calculated based on prior study of MORA Cure PFP (ClinicalTrials.gov., NCT05614583). In the exploratory clinical trial, the usual pain over the past week of full analysis set at 8 weeks post-treatment was 2.31 ± 1.49 for the experimental group and 3.18 ± 2.43 for the control group [35]. The calculated effect size (Cohen’s *d*) is as follows: $$d=\frac{{m}_{t}-{m}_{c}}{\sqrt{\left({s}_{t}^{2}+{s}_{c}^{2}\right)/2}}=\frac{2.31-3.18}{\sqrt{\left({1.49}^{2}+{2.43}^{2}\right)/2}}=-0.428$$, where $${m}_{t}$$ is mean of the experimental group, $${m}_{c}$$ is mean of the control group, $${s}_{t}$$ is standard deviation of the experimental group, and $${s}_{c}$$ is standard deviation of the control group [47]. Values were used up to the second decimal place, and the effect size was calculated without rounding.

Using an effect size of − 0.428, a Type I error of 0.05, and a power of 0.8, the formula for calculating the sample size per group is: $$n=\frac{2{\left({z}_{1-\alpha /2}+{z}_{1-\beta }\right)}^{2}}{{\left(d\right)}^{2}}=\frac{2{\left(1.960+0.842\right)}^{2}}{{\left(0.428\right)}^{2}}=86$$, where $$n$$ is required sample size per group (rounded up to the nearest whole number), $$\alpha$$ is Type I error, $$\upbeta$$ is Type II error (1 − power), and $$d$$ is effect size [47].

Considering a typical dropout rate of 10–30% for clinical trials involving digital services [48], a 20% dropout rate was assumed for this study. Adjusting for this dropout rate, the required sample size per group is calculated as: $${n}^{\text{'}}=86\times \frac{1}{1-r}=107.5$$, where *r* is the dropout rate (0.2). Thus, the target sample size is set at 216 participants in total, with 108 per group (Fig. 1).

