### Statistical methods for primary and secondary outcomes {20a}

For the definition of efficacy evaluation variables, see Table 1. Descriptive statistics (mean, standard deviation, median, minimum, maximum) will be presented for both experimental and control groups. Group differences will be analyzed using ANCOVA with baseline values as covariates, providing adjusted means (least square means), *p*-values, and 95% confidence intervals. Statistical tests will be two-sided with a significance level of 0.05, and results will include clinical interpretation.

Safety analysis will be conducted on the safety set. Adverse events (AEs) will be standardized by SOC and PT using the latest MedDRA version. Treatment-emergent adverse events (TEAEs) will be recorded as a single event per participant if they share the same SOC and PT, with severity classified by the highest severity reported, and causal relationship classified by the stronger link to the investigational device. Analysis will focus on TEAEs, including counts and percentages for TEAEs, knee-related TEAEs, adverse device effects (ADEs), and serious adverse events (SAEs). Percentage differences will be tested using Pearson’s chi-square test or Fisher’s exact test, if appropriate.

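### Effect modification by baseline pain is assessed only by a split at 50/49, which uses less of the data than an interaction with the continuous baseline already in the ANCOVA

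*Protocol article*

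**What the plan says.** The section on additional analyses {20b} of the protocol article gives the aim: "To determine whether the results of the primary efficacy evaluation differ according to subgroups of study participants". It names one analysis: "The subgroup analysis will compare participants with a usual pain intensity score over the past week at visit 2 of 50 points or higher", set against "to those with a score of 49 points or lower". It gives no reason for the value 50. It does not say whether the comparison is an interaction test or a set of separate tests. No other analysis of effect modification is described.

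The score being cut is fine-grained. Under Outcomes {12}: "Participants mark their pain level on a visual analog scale from 0 to 100, with values recorded and rounded to the nearest whole number". It is also already in the main model. Under the methods for primary and secondary outcomes {20a}: "Group differences will be analyzed using ANCOVA with baseline values as covariates", and "Statistical tests will be two-sided with a significance level of 0.05".

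Eligibility {10} sets no minimum pain score, and sequence generation {16a} rules out stratification. Nothing in the design therefore places 50 near the middle of the baseline distribution or makes the two subgroups similar in size.

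**The concern.** The question is whether the treatment effect changes with baseline pain. The split treats participants at 49 and 50 as different in kind, and those at 50 and 100 as the same. If the effect changes gradually along the scale, that discards information which the planned ANCOVA already holds for every participant. The further 50 lies from the centre of the distribution, the greater the loss.

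What is at stake is the quality of one supplementary answer: a wider interval and a smaller chance of seeing a real gradient. There is also a conditional risk. The method of comparison is left open, so the analysis could be carried out as two within-subgroup tests and read by which one is significant. That reading is unreliable when the true effect is the same in both.

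**Working it through.** **Inputs from the article.** Sample size {14} gives week-8 usual pain of "2.31 ± 1.49 for the experimental group and 3.18 ± 2.43 for the control group", a stated d of -0.428, "a Type I error of 0.05, and a power of 0.8", 20% dropout, and 86 evaluable or 108 randomised per group. The baseline distribution is not given, so its shape and the share at or above 50 are assumptions below and are shown as a range.

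**The plan's own figure.** n = 2(1.960 + 0.842)² / 0.428² = 85.7, so 86 per group. Then 86 / 0.8 = 107.5, so 108 per group and 216 in total. This reproduces. The printed means and SDs give d = -0.87 / √[(1.49² + 2.43²)/2] = -0.4316, hence n = 84.3, or 85. The difference of one per group has no bearing here.

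**Information kept by the split.** For a linear interaction, the efficiency of a dichotomised modifier relative to the continuous one is the squared correlation between the score and the indicator. Let p be the share at or above 50.

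- Normal baseline: φ(c)² / [p(1 - p)], where c is the cut in SD units from the mean.
- Uniform baseline: 3p(1 - p).

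| Assumed baseline | Share at or above 50 | Kept | Lost |
|---|---|---|---|
| Uniform | 50% | 0.750 | 25% |
| Uniform | 30% | 0.630 | 37% |
| Uniform | 20% | 0.480 | 52% |
| Normal | 50% | 0.637 | 36% |
| Normal | 30% | 0.576 | 42% |
| Normal | 25% | 0.539 | 46% |
| Normal | 15% | 0.426 | 57% |

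For example, the normal median cut gives 0.3989² / 0.25 = 0.637. The losses run from 25% to 57% over these cases. That is a range and not a bound: a normal baseline with only 10% at or above 50 would lose 66%.

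**Effect on interaction power.** Simulated ANCOVA with 172 participants and 4,000 runs. Assumed: baseline SD 20, and an interaction slope of 0.43 residual SD per baseline SD. Both models carry the continuous baseline as a covariate.

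| Assumed baseline mean | Continuous term | Split at 50 |
|---|---|---|
| 50 | 79% | 59% |
| 40 | 78% | 56% |
| 35 | 77% | 50% |

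With no interaction, both tests rejected in about 5% of runs.

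**The conditional risk: separate tests only.** Take the same true effect, d = 0.4316, in both subgroups, 86 evaluable per arm, and a two-sided 0.05 unadjusted t-test (noncentral t). With powers a and b, P(exactly one significant) = a(1 - b) + b(1 - a).

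| Per arm, by subgroup | Power a | Power b | Exactly one significant |
|---|---|---|---|
| 43 / 43 | 51% | 51% | 50% |
| 30 / 56 | 38% | 62% | 53% |
| 20 / 66 | 27% | 69% | 59% |

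The planned model is an ANCOVA, so these powers are approximate.

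**What the trial can detect either way.** The smallest difference between subgroup effects detectable with 80% power at an even split of 172 is (1.960 + 0.842) × √(4/86 + 4/86) = 0.85 SD, about twice the effect for which the trial is sized.

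**The case against.** The strongest reply is that the article fixes only a pre-specified cut, and that the rest is detail for a statistical analysis plan that is not shown. Much of this stands.

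- A reader might infer that the trial will test each subgroup separately and report success in one only. The article does not say so. Its aim sentence fits an interaction test, and such a test on the split keeps its error rate at 5%. The 50% to 59% figures describe one possible implementation.
- A reader might also take the word compare literally, as setting the week-8 pain of high-pain participants against that of low-pain participants. That would not address effect modification, but the preceding aim sentence makes the reading unlikely.
- It is tempting to say that the split always discards a third or more of the information. That holds for a normal baseline and a linear interaction. A uniform baseline cut at its median loses 25%, and if the effect really changed at a threshold near 50, the split would not be the weaker choice.
- Nothing in the article ties the subgroup result to labelling or to a decision rule, so a claim that it would misdirect the device's indication is not supported. There is one subgroup factor with a fixed cut, so neither a data-driven cut nor a multitude of subgroups is at issue.

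What the reply does not remove is that the article states the dichotomy itself as the method. This is a choice made in the text and not an omission, and a better use of the same data is at hand.

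**Conclusion.** The point holds as a minor matter of efficiency. The only stated analysis of effect modification cuts a whole-number 0-100 score at 50/49, although that score is already an ANCOVA covariate. For a roughly linear interaction, the cut loses about 25% to 57% of the information in the cases worked, even when it is tested properly. The exact loss depends on a baseline distribution that the article does not give. A false single-subgroup finding is a risk only under separate within-subgroup tests, so it should not be reported as a defect of the plan as written.

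**What to change.** Before the database is locked, state that effect modification by baseline usual pain will be judged in a supplementary model: the primary ANCOVA plus an arm by continuous baseline usual pain term. Base the conclusion on that term and its 95% CI. Keep the 50/49 split to display the treatment effect and its 95% CI in each subgroup, without within-subgroup p-values.

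The cost is one model term and a sentence or two of text, with no new data or participants. The term brings a linearity assumption, which should be stated. It will still have low power for modest interactions, so an inconclusive result should not be read as evidence that the effect is constant.

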### Plans to give access to the full protocol, participant-level data, and statistical code {31c}

There are no plans to give access to the full protocol, participant-level data, and statistical code.

## Oversight and monitoring

### Composition of the coordinating center and trial steering committee {5d}

The investigators will hold investigator meetings as needed, led by two experienced orthopedic surgeons who have been assigned the role of coordinating investigators. Information regarding the protocol and the device must be provided to the investigators prior to the start of the trial, and formal acceptance must be obtained. Before the trial begins, the sponsor will visit each site for a site initiation visit (SIV), where the research team will be briefed on the trial, and the final operational details will be confirmed. If necessary, a site feasibility meeting may be conducted prior to the SIV meeting.

The sponsor and CRO will hold monthly meetings to review the progress of the study and discuss any issues that arose during routine monitoring visits. If necessary, additional QC visits, individual investigator meetings, or investigator group meetings may be scheduled to address specific concerns or ensure the smooth continuation of the trial.

### Composition of the data monitoring committee, its role and reporting structure {21a}

This study does not include a data monitoring committee (DMC). The decision to exclude a DMC is based on the fact that the study involves minimal risk to participants, and the investigational medical device has already demonstrated a favorable safety profile in prior studies. Additionally, the study design allows for close monitoring by the investigators and sponsor through regular site visits and data reviews, ensuring that participant safety and data integrity are adequately maintained without the need for an independent monitoring committee.

### Adverse event reporting and harms {22}

All adverse events that occur or worsen after obtaining the subject’s consent will be collected, except for those who fail the screening. Pre-existing signs or symptoms at the time of consent are recorded in the medical history section of the CRF. AEs should be monitored until symptoms resolve and the condition stabilizes, and progress reports may be required by the sponsor. The investigator should provide a clear diagnosis, or otherwise record symptoms/signs. Appropriate examinations and treatments must be administered for all AEs. If an AE makes it difficult to continue the trial, the subject may drop out or the trial may be discontinued, with the best treatment provided for safety.

The CRF must record whether the AE is treatment-emergent (TEAE), the onset and end dates, severity, causal relationship with the investigational device, actions taken, and outcome. Serious adverse events (SAEs), serious adverse device effects, and unexpected adverse device effects must be reported to the IRB and regulatory authorities within the required timeframes. Specific AEs, such as worsening knee pain, cramps, dizziness, changes in mood or thought patterns, and any other significant AEs, must be documented and shared with the sponsor within 24 h.

All adverse events that occur will be standardized using System Organ Class (SOC) and Preferred Term (PT) with the latest version of MedDRA. Treatment emergent adverse events (TEAEs) that occur after application of the investigational medical device will be counted as one event when the same SOC and PT adverse event occurs multiple times in one subject, and when the severity differs for the same adverse event, it will be handled with the maximum severity. When the causal relationship differs for the same TEAE in one subject, it will be handled in the direction of higher relatedness to the investigational medical device. Summary and analysis of adverse events will be performed for TEAEs. The number of subjects experiencing events, incidence rates, and number of events will be presented for TEAEs, knee-related TEAEs, ADEs, and SAEs.

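### The once-per-term rule for repeat adverse events is also applied to the reported number of events, so that total under-states occurrences whenever a term recurs

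*Protocol article*

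**What the plan says.** Two sections of the protocol article give the same counting rule. Under Adverse event reporting and harms {22}, a TEAE "will be counted as one event when the same SOC and PT adverse event occurs multiple times in one subject"; differing severities are resolved to the highest and differing causality assessments to the most device-related. Under Statistical methods for primary and secondary outcomes {20a}, TEAEs "will be recorded as a single event per participant if they share the same SOC and PT", with the same treatment of severity and causality.

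The outputs are described less uniformly. The harms section promises three results: "The number of subjects experiencing events, incidence rates, and number of events will be presented for TEAEs, knee-related TEAEs, ADEs, and SAEs". The statistical section speaks of an analysis "including counts and percentages for TEAEs, knee-related TEAEs, adverse device effects (ADEs), and serious adverse events (SAEs", and adds that "Percentage differences will be tested using Pearson’s chi-square test or Fisher’s exact test, if appropriate".

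On collection, the harms section says: "All adverse events that occur or worsen after obtaining the subject’s consent will be collected, except for those who fail the screening". Onset and end dates, severity, causality, actions and outcome are entered on the CRF. Neither section restricts the once-per-term rule to participant counts, and neither gives a separate definition of the number of events.

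**The concern.** Collapsing repeats of a term within a participant, and keeping the worst severity and the strongest causal link, is the right convention for the number and percentage of participants affected. Here it is written as the rule for counting events, and the number of events is then listed as a result of its own. Reporting participants and events side by side is useful mainly because events can exceed participants when a problem recurs. The rule removes that information.

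The kinds of event singled out for prompt notification make this relevant: "Specific AEs, such as worsening knee pain, cramps, dizziness, changes in mood or thought patterns, and any other significant AEs". Some of these could recur in people exercising daily for 8 weeks, although the article itself says nothing about how often. A participant with one flare of knee pain and a participant with five would each add one to the knee-related event total. A repeat adverse device effect, or a repeat serious event coded to the same term, would likewise add nothing. What is at stake is the accuracy of one set of published safety totals in a confirmatory trial whose stated aim includes safety.

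**Working it through.** **Plan's own figure.** The article states no event rate and no expected event count, so there is no figure to reproduce. The check is textual first, then illustrative.

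**Step 1: apply the rule as written.** Suppose a participant has k occurrences of one preferred term, with k at least 1.

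- Contribution to the number of participants: 1.
- Contribution to the number of events under the rule: 1.
- Contribution if every occurrence is counted: k.

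So for one preferred term the promised event total always equals the participant total.

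**Step 2: aggregates over several terms.** Take a participant with two different knee-related terms, one occurring three times and the other once. The participant count is 1, the event count under the rule is 2, and the occurrences are 3 + 1 = 4. In the aggregate categories the event count can therefore exceed the participant count, but only through different terms, never through recurrence.

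**Step 3: size, under an assumption.** Assume that occurrences of one term are Poisson with mean m per participant. The value of m is not in the article. Take n = 108 per arm from Sample size {14}.

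- Occurrences: n × m
- Events under the rule: n × (1 − exp(−m))
- Share lost: 1 − (1 − exp(−m)) / m

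| m (assumed) | Occurrences per arm | Events under the rule | Share lost |
|---|---|---|---|
| 0.1 | 10.8 | 10.3 | 4.8% |
| 0.5 | 54.0 | 42.5 | 21.3% |
| 1 | 108.0 | 68.3 | 36.8% |
| 2 | 216.0 | 93.4 | 56.8% |

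**Step 4: effect on a comparison of event totals.** If the arms had means of 1.0 and 0.5, the true ratio of occurrences would be 2.0. Under the rule it would be 68.3 / 42.5 = 1.61. With means of 2 and 1 it would be 93.4 / 68.3 = 1.37. The direction is kept and the ratio shrinks.

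**Step 5: what does not move.** The number and percentage of participants with an event depend only on whether k is at least 1, so the rule leaves them unchanged. The chi-square and Fisher tests compare those percentages and are unchanged too.

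**The case against.** The strongest reply is that nothing inferential depends on this total. The only between-group safety test compares percentages, for which once per term is correct. That stands, and it limits the point to a descriptive output.

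Second, recurrences are not lost from the trial. All adverse events are collected with dates, serious and unexpected device effects go to the IRB and authorities, and the named events go to the sponsor within 24 hours. That also stands: the loss is from a summary table, and it can be recovered from the CRF.

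Third, the aggregate totals are not empty, since one participant can contribute several terms (Step 2), and they follow a disclosed definition. This is true, but a reader of a table headed number of events would take it to mean occurrences, and the rule gives something else.

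Fourth, once-per-term wording is familiar for participant-level tables, and an unseen statistical analysis plan may fill the event column differently. A drafting slip is indeed the likelier explanation. But this is not a detail left open: both sections state the rule for events, and a plan that counted every occurrence would depart from that wording.

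Fifth, occurrence counts have weaknesses of their own. Participants enter with pain of more than 3 months' duration, so dividing fluctuating knee pain into separate events is partly arbitrary. Adverse event review may also be omitted when visit 3 is remote (Participant timeline {13}), which can leave no scheduled review between baseline and the post-treatment visit at 8 to 9 weeks. This is a fair caution about interpreting the count, not a reason to label participant-by-term pairs as events.

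A reader might go further and infer that the rule hides a safety difference between arms, or that having no data monitoring committee makes it worse. The documents support neither. The formal comparison is unaffected, no recurrence rate is given, and the rule governs a summary made after database lock with no interim analysis planned, so it plays no part in ongoing oversight.

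**Conclusion.** The point holds for one output. As written, the reported number of events for TEAEs, knee-related TEAEs, adverse device effects and serious adverse events is a count of participant-by-term pairs, and it falls short of the number of occurrences whenever a term recurs in a participant. That conclusion rests on the text alone.

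The size does not. It depends on a recurrence rate that the article does not give and on the Poisson assumption. The shortfall is about 5% at a mean of 0.1 occurrences per participant, 21% at 0.5 and 37% at 1. Higher losses require a term to recur more often than that, and nothing in the article suggests that it will. At low rates the effect is small.

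Participant counts, percentages, the between-group tests, raw collection, expedited reporting and the efficacy analysis are all unaffected. This is a correction to safety reporting that is worth making because it is cheap, not a threat to the trial's conclusions.

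**What to change.** In both sections, limit the once-per-SOC-and-PT rule, with maximum severity and strongest relatedness, to the number and percentage of participants. Then define the number of events as all separately recorded occurrences, shown by arm beside the participant counts for each of the four categories. Suitable wording would be: *For participant counts and percentages, a participant is counted once per SOC and PT, at the highest severity and strongest relatedness recorded. The number of events counts every separately recorded occurrence.*

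The cost is a sentence in each of two sections and the way one table column is filled. The CRF already records onset and end dates, so no new data are needed, and the change can be made before database lock.

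There is a small downside. The occurrence count will depend on how sites split fluctuating knee pain into dated episodes, and on recall where adverse event review is omitted at a remote visit 3. A table footnote should say so, and the count should remain descriptive.
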